**Fig. 1 Fig1:**
[figure not shown]
Consolidated Standards of Reporting Trials statement extension for social and psychological interventions (CONSORT-SPI) flow diagram. Diagram of participant (hospital networks) recruitment. *Numbers to be incorporated as trial progresses

A parallel, cluster randomised trial will be used to test for differences between a theory-based implementation approach (TDFI) and a non-theory based implementation approach to improving LS referral practices in eight large Australian hospital networks across three states [New South Wales (n=4), Victoria (n=2), and Western Australia (n=2)]. As sharing of staff and resources in networked hospitals is likely to lead to correlations between outcomes, each hospital network will comprise a separate cluster in this trial (i.e. eight clusters in total). Hospital networks will be randomly allocated to the theory arm or non-theory arm using a computer-generated random sequence. To account for differences in region-specific LS detection pathways, the randomisation will be stratified by participating states, with the same number of networks from each state allocated to theory and non-theory arms (a 1:1 allocation ratio). A theory-based, mixed methods process evaluation will be conducted alongside the trial to investigate intervention fidelity, potential mechanisms of impact, mediators and contextual moderators, for both approaches [24, 36].

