#### Assessing clinical practice change

The analysis of each dichotomous study outcome will be conducted at the individual patient level, using generalised estimating equation (GEE) adjustment for the clustering of patients within hospital networks. We will estimate the adjusted relative proportion (RR) of patients with the outcome using a generalised linear regression model with Poisson distribution, log link and robust standard errors. The exposure variable will be the implementation intervention status of the respective hospital network at the time of the patient’s CRC resection (pre or post implementation-intervention). We will carry out a two-sided test for each outcome, with the significance threshold defined using the Bonferroni correction for the number of outcomes tested. Missing testing and/or referral data will be treated as tests not carried out, or referral not completed, respectively. As covariates, we will consider time period (3-month intervals), time since implementation of intervention strategies (3-month intervals), patient age at operation, sex and cancer stage. The Quasi-Akaike information criterion will be used to select which covariates to include in the final model. To account for non-independence of within-hospital outcomes, all GEE analyses will be carried out with exchangeable working correlation structures. We will carry out sensitivity leave-one-out analyses by individually excluding hospital networks that accounted for more than 20% of the total patient numbers. If private patient status can be reliably obtained in at least six of eight trial sites, a supplementary analysis will be performed using private patient status as an additional covariate.

We note previous studies have found that a small number of clusters can lead to inflated type I error rates, and so-called small-sample corrections have been proposed to address this. However, these small-sample corrections were found to be too conservative for eight clusters [46]. Consequently, we will carry out a supplementary analysis using small-sample correction only for those outcomes that are robustly significantly associated with the implementation intervention status.

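### With eight clusters, inference rests on uncorrected robust standard errors, and a small-sample correction is only a supplement for outcomes already significant

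*Protocol article*

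**What the plan says.** The Design section of the protocol article fixes the number of clusters: "each hospital network will comprise a separate cluster in this trial (i.e. eight clusters in total", allocated by state "with the same number of networks from each state allocated to theory and non-theory arms (a 1:1 allocation ratio".

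The section Assessing clinical practice change sets the analysis. Each dichotomous outcome is modelled at patient level "using a generalised linear regression model with Poisson distribution, log link and robust standard errors", and "all GEE analyses will be carried out with exchangeable working correlation structures". The effect tested is a pre/post contrast: "The exposure variable will be the implementation intervention status of the respective hospital network". Tests are two-sided at a Bonferroni threshold, with no number given for the level or for how many outcomes count. No reference distribution is named.

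The same section then addresses the small number of clusters. It notes that "a small number of clusters can lead to inflated type I error rates", reports from a cited source that "these small-sample corrections were found to be too conservative for eight clusters", and concludes that "we will carry out a supplementary analysis using small-sample correction only for those outcomes that are robustly significantly associated with the implementation intervention status".

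**The concern.** The robust (sandwich) variance is justified by a large number of clusters. With eight it tends to be too small, and a normal critical value ignores how variable it is. Both faults make p-values too small and confidence intervals too narrow. The protocol recognises this but still rests each outcome's inference on the uncorrected result.

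Three things follow. The error rate behind a declared effect would exceed the nominal one. A disagreement between the uncorrected and corrected results would have no prespecified resolution. Outcomes that miss significance would never receive a corrected interval, so a null or inconclusive result would look more precise than it is. Bonferroni does not repair this, because the ratio of actual to nominal error grows further into the tail.

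**Working it through.** **No figure to reproduce.** The protocol states no numeric level, sample size or power, so the check estimates the error rate of the rule as written.

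**Inputs from the protocol article**
- 8 networks, 4 per arm (Design).
- 100–250 resections per network per year (Study site recruitment), drawn as uniform.
- 24 months before (Pre-implementation outcomes) and up to 9 months after (Clinical data collection), so 2 and 0.75 times the annual number.
- Poisson GEE, log link, robust standard errors, exchangeable correlation, two-sided test (Assessing clinical practice change).

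**Assumptions, because the protocol gives no value**
- Level 0.05, or 0.05/4 = 0.0125 if the one primary and three secondary outcomes are all counted.
- Baseline proportion 0.3–0.7, intra-cluster correlation 0.01–0.10, cluster autocorrelation 0.5–1.0.
- No covariates.

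**Step 1: approximation.** Take the statistic as t with df = 8 − 1 = 7 for pre/post, or 8 − 2 = 6 for an arm-by-period contrast. Refer it to the normal critical value z, first as it stands and then with z multiplied by √(df/8) to reflect the downward bias of the sandwich variance.
- Level 0.05, z = 1.960. For 7 df: P(|t| > 1.960) = 0.091; with bias, 1.960 × √(7/8) = 1.833, giving 0.109. For 6 df: 0.098 and 0.141.
- Level 0.0125, z = 2.498. For 7 df: 0.041 and 0.052. For 6 df: 0.047 and 0.074.

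**Step 2: simulation under no effect.** Five assumption sets, 3,000 trials each, Monte Carlo standard error about 0.002–0.006. The entries are the range of rejection rates over the five sets.

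| Test | Pre/post, 0.05 | Pre/post, 0.0125 | Arm-by-period, 0.05 | Arm-by-period, 0.0125 |
|---|---|---|---|---|
| Uncorrected, normal | 0.109–0.125 | 0.051–0.062 | 0.133–0.154 | 0.069–0.080 |
| Uncorrected, t | 0.063–0.073 | 0.015–0.022 | 0.073–0.083 | 0.022–0.029 |
| Kauermann-Carroll, t | 0.049–0.058 | 0.011–0.017 | 0.043–0.054 | 0.007–0.017 |
| Mancl-DeRouen, t | 0.038–0.045 | 0.006–0.012 | 0.028–0.034 | 0.003–0.009 |
| Uncorrected normal and Kauermann-Carroll t both significant | 0.049–0.058 | 0.011–0.017 | 0.043–0.054 | 0.007–0.017 |

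The pre/post columns are the test that the protocol writes. It writes no arm term, so the arm-by-period columns show only what would happen if one were added under the same rule.

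**Step 3: ratios to nominal**
- Pre/post, normal reference: 0.109/0.05 = 2.2 to 0.125/0.05 = 2.5; 0.0513/0.0125 = 4.1 to 0.0617/0.0125 = 4.9.
- Pre/post, t reference: 0.0147/0.0125 = 1.2 to 0.022/0.0125 = 1.8, with the 0.05 results inside that range.
- Arm-by-period, normal reference: 2.7 to 3.1 at 0.05 and 5.5 to 6.4 at 0.0125. With t: 1.5 to 2.3.

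**Step 4: what Bonferroni leaves.** If four outcomes were independent, the pre/post family-wise error would be 1 − (1 − 0.0513)^4 = 0.19 to 1 − (1 − 0.0617)^4 = 0.22, against an intended 0.05. The outcomes share patients, so this is illustrative.

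**Step 5: interval width.** A nominal 95% interval from the uncorrected normal test would cover a null pre/post effect in 1 − 0.125 = 87.5% to 1 − 0.109 = 89.1% of trials.

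**Step 6: the trigger.** The last table row equals the Kauermann-Carroll row. An outcome significant under Kauermann-Carroll with t was always significant under the uncorrected test too, so correcting only after significance adds no false positives provided the corrected result decides.

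**The case against.** Several points on the other side stand.

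- The protocol discloses the inflation risk and gives a sourced reason for its choice. The source is not available here, and the simulation partly agrees with it: Mancl-DeRouen with t is conservative. One can say only that the reason does not extend to every correction, not that the source is wrong.
- An article may leave the reference distribution and degrees of freedom to the analysis plan. If a t reference is intended, most of the excess disappears, though not all of it.
- The simulation is not the full planned model. The protocol allows calendar time, time since implementation, age, sex and stage, chosen by a quasi-Akaike criterion. Neither covariates nor selection were simulated, and baseline rates and between-network variation are assumed because the protocol says they are unknown.

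Two stronger readings are tempting. A reader might infer that a stated alpha is exceeded six-fold. The protocol states no number, and about six-fold arises only for an arm-by-period contrast at 0.0125 with a normal reference, a test that the protocol does not write. A reader might also infer that correcting only after significance itself inflates the error. Step 6 shows that it does not.

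None of this removes the core. The protocol does not leave the role of the correction open: it fixes it as supplementary and conditional. Conservatism in some corrections does not justify a deciding test that runs above its nominal level.

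**Conclusion.** The concern holds in this form: an uncorrected robust GEE on eight clusters carries the inference, correction is a conditional supplement, and nothing says which result prevails.

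For the pre/post test as written, type I error is about 2 to 5 times nominal with a normal reference and about 1.2 to 1.8 times with t. For an arm-by-period contrast, were one added, the figures are up to about 6 times and 1.5 to 2.3 times. All rest on an assumed level of 0.05 to 0.0125, assumed baseline rates and correlations, and a model without covariates.

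The inflation is due to the uncorrected test deciding. The separate harm of the trigger is that non-significant outcomes keep intervals that are too narrow. Kauermann-Carroll with t was close to nominal under these assumptions, so a usable correction appears to exist at eight clusters; this has not been shown for the covariate-selected model.

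**What to change.** Prespecify one small-sample-corrected analysis as the deciding inference. One suitable choice is the Kauermann-Carroll variance with a t reference, with df equal to the number of networks minus the number of network-level parameters. Report its p-values and confidence intervals for every outcome, significant or not, and show the uncorrected GEE as supplementary. State the numeric level and the number of outcomes in the Bonferroni correction. Once baseline data give the rates and correlations, repeat the null simulation with the planned covariates and selection step to confirm the choice.

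The cost is a change of wording, a few lines of code, wider intervals and somewhat lower power. As a guide to width for pre/post in a balanced case, the 95% critical value rises from 1.960 to 2.365 (t, 7 df) and the standard error by √(8/7) = 1.069, so the interval on the log scale is about (2.365/1.960) × 1.069 = 1.29 times as wide. The power calculation, which the protocol defers until baseline data are in, should use the corrected test. The Trial status section reports that data collection had not begun, so the change could be made before any outcome data are seen.

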### Trial status

This study commenced in July 2017. Hospital networks have been approached to participate, have been randomised and are engaged in the governance process. Formal recruitment of hospital networks will be complete when research governance applications are approved. Recruitment of individual participants for the research activities described in phases 1–7 has not commenced, and data collection has not commenced.

## Discussion

The implementation of a systematic approach to LS identification and referral is complicated, and requires behavioural change amongst a multidisciplinary team of healthcare professionals working within a complex and unpredictable system. Results from the pilot study highlighted a number of theoretical and practical issues related to using a theory-based implementation approach to addressing the LS referral problem in this context - a possible explanation for the lack of improvement in referral overall [30]. By engaging someone from within the system to lead the implementation approach we seek to overcome these issues, enabling us to determine the extent to which the use of theory-based implementation approaches are (1) feasible in this setting and (2) more effective than approaches reliant on the intuition and tacit knowledge of healthcare professionals.

In addition to addressing a known clinical problem, this will be the first study to compare the effects of two implementation approaches, distinguished only by the use of theory to determine psychosocial barriers and intervention development to translate evidence into practice in complex healthcare systems. By analysing clinical practice data pre-post intervention, we will determine the more effective approach for increasing the proportion of patients with CRC with risk-appropriate completion of the LS referral and testing pathway, and the difference in the types of strategies generated through theory-driven and intuitive approaches taken to achieve this. This will also build on the work of Brennan and colleagues [11] to enhance understanding of LS referral and diagnostic practices in Australia.

Limitations of this study include an inability to control for differences between sites at individual, system and organisational levels, reflecting the real-world challenges of implementing practice-change interventions across diverse and unpredictable healthcare systems. These challenges emphasise the crucial need to study implementation trials to understand what works, in what contexts, why and at what costs [33]. The process evaluation, by providing valuable information for both approaches about intervention fidelity, potential mechanisms of impact, mediators and contextual moderators, will enable generalisability [24]. Time, resource and cost data will also be collected and incorporated into a microsimulation model (*Policy1*; currently validated for cervical [47] and bowel cancer [48] and undergoing development for LS^1^), as part of an economic evaluation to determine the most cost-effective approach.

Results from this study will not only guide the development of future interventions to improve LS identification on a larger scale and across different contexts, but also interventions to translate evidence-based practice changes from the rapidly evolving field of genomic research into complex, dynamic healthcare systems. Results will be shared within participating healthcare systems, and to the wider community. We will also contribute to the evolving Behaviour Change Technique Taxonomy [49], and to the behavioural change and implementation science community in advancing understanding on how to promote the effective use of implementation strategies to enhance uptake of evidence-based research.

## Data Availability

The datasets (subject to ethics committee and individual hospital governance requirements), data management procedures and training materials used throughout the trial are held at the Cancer Council NSW and will be available from the corresponding author on reasonable request following trial completion.

## Abbreviations

CONSORT-SPI: Consolidated Standards of Reporting Trials statement extension for social and psychological interventions
CRC: Colorectal cancer
FCC: Familial cancer clinic
GEE: Generalised estimating equation
IPSBQ: Influences on Patient Safety Behaviours Questionnaire
LS: Lynch syndrome
MMR: Mismatch repair
MSI: Microsatellite instability
RR: Adjusted relative proportion
SPIRIT: Standard Protocol Items: Recommendation For Interventional Trials
TDF: Theoretical domains framework
TDFI: Theoretical domains framework implementation
